### Trial design and randomization

The initial user group of existing providers (*n* = 1640) were randomized 1:1:1 to the three study arms on April 6, 2021. Each time the ordering provider subsequently placed orders to prepare or transfuse pRBC, the provider remained in the same arm as per the initial randomization. In the baseline data examined, the number of pRBC transfusion events ordered was highly variable between providers. To balance providers with high and low ordering behavior, providers were randomized in blocks based on their ordering behavior at baseline. The average monthly ordering rate for each provider was calculated and the distribution of average monthly ordering rates divided into groups by quartile. Providers were then block randomized according to their average monthly ordering rate quartile group. All eligible providers who started at UCH after the initial randomization were similarly allocated 1:1:1 to one of the three study arms. This study was classified as quality improvement and thus non-human subject research so did not require informed consent from providers to enroll in the intervention arms per the study site’s institutional review board (IRB). No identifying images or other personal or clinical details of providers or patients are included here or will be presented in reports of the trial results. This trial does not involve collecting biological specimens for storage. There is no anticipated harm or compensation for trial participation. The project management group is composed of all authors listed in this trial. A subset of the authors met regularly to review trial progress and were responsible for monitoring trial results every 6 months to evaluate outcomes data. An interim analysis was conducted every 6 months to implement a-priori specified stopping criteria, specifically a 20% effect size as described below. The authors met with EHR analysts to implement the order set changes before the start of the trial. Day-to-day EHR support for providers is provided through the EHR help desk. EHR help desk personnel could reach out to the principal investigator for questions. This intervention was considered low-risk, and therefore, a data monitoring committee was not considered.

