#### Treatment comparisons

The a priori primary objective comparison is between the group using the new interface (arm 1) and the two groups using the new interface with non-interruptive or interruptive alerts combined (arms 2 and 3, respectively).

If the a priori primary objective comparison is statistically significant, we will further test the secondary comparison for differences in compliance between the different alert groups, arm 2 versus arm 3.

We will conduct an exploratory comparison of the historical pre-trial data to the post trial onset data. If the primary objective comparison is statistically significant, we will compare the pre-trial data to arm 1 and then 2 and 3 combined. If the primary objective comparison is not statistically significant (no difference across arms), we will compare the pre-trial data to arms 1, 2, and 3 combined.

Hypothesis testing for both primary and secondary comparisons of the trial data will be implemented using generalized linear mixed models with the binary outcome of guideline-concordant order, group comparison(s) as a fixed effect, and a random intercept for provider. Significance testing will be set at *p* < 0.05.

The comparison of historical pre-trial data versus the post-trial onset data will be implemented using generalized linear mixed models with the binary outcome of guideline-concordant order (yes/no). We will implement an interrupted time series analysis by parameterizing this model with fixed effects including an intercept, a term for post-trial onset (intercept shift), a linear time trend, and an interaction between post-trial onset and linear time trend (slope difference). Pre-trial data is available for two years prior to the trial onset. The COVID pandemic likely affected the outcome of interest. If there are notable effects on the pre-trial (but post COVID onset) trend in guideline-concordant ordering, we will exclude the immediate period post-COVID from the historical pre-trial trend estimation.

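### The stated primary model leaves out the blocking quartile and the pre-trial concordance already held: it is valid but gives up precision, by an amount the documents cannot fix

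*Protocol article*

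**What the plan says.** All references are to the protocol article.

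- **Primary and secondary model** (Treatment comparisons): a generalized linear mixed model for guideline-concordant order, with "group comparison(s) as a fixed effect, and a random intercept for provider". No covariate is named here or elsewhere.
- **Randomisation** (Trial design and randomization): "The average monthly ordering rate for each provider was calculated and the distribution of average monthly ordering rates divided into groups by quartile". Then: "Providers were then block randomized according to their average monthly ordering rate quartile group".
- **Later starters** (same section): "All eligible providers who started at UCH after the initial randomization were similarly allocated 1:1:1 to one of the three study arms". Their number is not given.
- **Pre-trial data** (Treatment comparisons): "Pre-trial data is available for two years prior to the trial onset". They serve only the exploratory before/after analysis, with the same outcome: "The comparison of historical pre-trial data versus the post-trial onset data will be implemented using generalized linear mixed models with the binary outcome".
- **Provider variation** (Discussion, limitations): the answer given is the hierarchical model together with blocking on ordering frequency.

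**The concern.** The design balances arms on ordering rate, but the model does not carry that factor. If ordering rate predicts concordance, omitting it leaves the standard error too large for the design actually used, so the precision bought by blocking goes unclaimed. A provider's own earlier concordance is a natural predictor of later concordance. It can be computed from data in hand for any provider with pre-trial orders.

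Precision matters here for three reasons:

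- Statistical power puts power for a 10% effect at 52 weeks at only 64%, from a logistic regression in which no provider effect is described.
- Arm 2 versus arm 3 is tested only if the primary comparison is significant.
- Trial status says the trial stopped because the 12-month analysis showed no significant difference. The width of the interval then decides what can be concluded.

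**Working it through.** **1. The plan's own power figures.** The stated values are 64% (10% effect, 52 weeks), 80% (15%, 35 weeks) and 80% (20%, 19 weeks).

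- Inputs from Statistical power: hemoglobin normal with mean 8.3 and SD 1; ordering probability 1, 0.2 and 0.08 in the three bands; 228 providers, 30% at 3 and 70% at 1 encounter a day.
- Orders per encounter: 0.0968 × 1 + 0.2853 × 0.2 + 0.6179 × 0.08 = 0.203.
- Encounters per day: 228 × (0.3 × 3 + 0.7 × 1) = 364.8. Orders per day: 364.8 × 0.203 ≈ 74, not the 30 to 35 the section assumes.
- Two-proportion power, two-sided 0.05, is 98%, over 99% and over 99% at 74 orders a day, and 73%, 90% and 90% at 30 a day. The stated values need about 22 to 24 a day.

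The figures therefore do not reproduce. That is a separate matter. The steps below use 30 orders a day.

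**2. Variance of the arm effect.** For provider i with mᵢ orders, the estimated log-odds has variance

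vᵢ = τ² + 1/(mᵢ p(1−p)), with τ² = ICC/(1−ICC) × π²/3.

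A baseline covariate with correlation r to the provider's trial-period log-odds reduces τ² to τ²(1−r²). With I = Σ 1/vᵢ and a 1:2 comparison, Var(arm effect) = (3 + 1.5)/I = 4.5/I. Here p = 0.51; p(1−p) is close to 0.25 for any share near one half. Total orders are 30 × 364 = 10,920.

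*Worked case: 228 providers, ICC 0.05, r = 0.5.*

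- 68 high-frequency providers place 90 orders each (sampling variance 0.0445) and 160 low-frequency providers place 30 each (0.1334).
- τ² = 0.1732; after adjustment 0.1732 × 0.75 = 0.1299.
- Unadjusted: I = 68/0.2177 + 160/0.3066 ≈ 834, so SE = √(4.5/834) = 0.0734.
- Adjusted: I = 68/0.1744 + 160/0.2633 ≈ 998, so SE = 0.0672.
- Variance ratio: 834/998 = 0.836.
- A 15% reduction is a log odds ratio of ln(1/0.85) = 0.1625. Power is Φ(0.1625/SE − 1.96): 60% unadjusted, 68% adjusted.

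**3. Range of variance ratios (adjusted/unadjusted), 52 weeks, baseline for all.**

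| Providers | ICC | r = 0.3 | r = 0.5 | r = 0.7 |
|---|---|---|---|---|
| 228 | 0.02 | 0.959 | 0.886 | 0.774 |
| 228 | 0.05 | 0.941 | 0.836 | 0.676 |
| 228 | 0.10 | 0.929 | 0.803 | 0.612 |
| 1640 | 0.02 | 0.989 | 0.969 | 0.939 |
| 1640 | 0.05 | 0.977 | 0.937 | 0.874 |
| 1640 | 0.10 | 0.965 | 0.901 | 0.803 |

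The reduction is thus about 4 to 39% with 228 providers and about 1 to 20% with 1640, keeping the same 30/70 mix. At ICC = 0, τ² is zero and nothing is gained.

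With 228 providers and r = 0.5, power for the 15% effect at 52 weeks goes from 82% to 86% (ICC 0.02), 60% to 68% (0.05) and 39% to 47% (0.10).

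**4. Missing baselines.** If 30% of providers have none, the r = 0.5 ratios with 228 providers become 0.92, 0.88 and 0.85.

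**5. What was not calculated.** No calculation tests the quartile term: the documents do not relate ordering rate to concordance.

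**The case against.** The strongest reply is that nothing here is an error. The model allows for clustering by provider, as provider randomisation requires. The Discussion recognises provider variation and answers it, and an article may leave covariates to a fuller plan. The first part stands: this is a loss of efficiency, not a bias or an invalid test. The last part is weaker. The same section lists the fixed effects of the interrupted time series term by term, so the authors name fixed effects where they intend them.

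A reader might infer more than the documents support:

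- *That between-provider variation dominates the noise.* No ICC is given. With 1640 providers the mean is 10,920/1640 = 6.7 orders each, with sampling variance of about 1/(6.7 × 0.25) = 0.60. That exceeds τ² across the assumed range (0.067 to 0.366).
- *That a high r can be taken for granted.* Two years at 30 a day is about 21,900 orders, or 13 per provider over 1640, so many baselines would be noisy. The baseline also comes from an interface whose multi-unit buttons were removed in every arm, and units ordered enter the outcome. The plan itself expects COVID to have affected the pre-trial outcome.
- *That most existing providers have a usable baseline.* No count is given.
- *That the quartile is prognostic.* It measures volume, and no link to concordance is shown.
- *That the null result follows from the omission.* At ICC 0.02 with 228 providers, unadjusted power for a 15% effect at 52 weeks is already 82%.

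Finally, the 12-month primary result has been seen. Quietly replacing the stated model now would be a post-hoc switch. That objection stands, and it shapes the fix.

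**Conclusion.** The point holds as one of precision. The stated model is valid but omits the factor used to block randomisation and a pre-randomisation measure of the outcome that is already held. Most of any gain should come from baseline concordance. The case for the quartile is that the analysis should reflect the design; leaving it out makes the standard error conservative only if ordering rate is prognostic.

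The direction is clear whenever providers differ and past concordance carries some information about later concordance. The size is not: it rests on an assumed ICC and r, on 30 orders a day, and on how orders are spread over providers. It could be trivial (about 1%) or material (up to about 39% of the variance). The change is worth making because the data exist, but no single power figure should be quoted for it.

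**What to change.** Specify an adjusted mixed model for the primary and secondary comparisons with:

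- the arm contrast;
- the randomisation stratum: four ordering-rate quartiles plus a category for providers with no baseline, such as those who joined after April 6, 2021;
- the provider's pre-trial concordance as a shrunken logit, set to the mean where there is none;
- the provider random intercept, as now.

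Fix the shrinkage rule and the pre-trial window, including how the COVID period is handled. Because interim results are known, date the specification before any further analysis and report this model beside the unadjusted model stated in the article, whichever is more favourable. Report the observed ICC, the baseline-to-trial correlation and the number of providers without a baseline, so that readers can judge the gain.

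The cost is a few extra fixed effects and a rule for missing or sparse baselines, with no new data collection. Since the stated model is already conditional on provider, adding provider-level covariates should barely change the odds ratio being estimated.

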**Methods:**

All inpatient providers at University of Colorado Hospital (UCH) who order blood transfusions were randomized in a 1:1:1 fashion to the three arms of the study: (1) general order set improvements, (2) general order set improvements plus non-interruptive in-line help text alert, and (3) general order set improvements plus interruptive alert. Transfusing providers received the same randomized order set changes for 18 months. The primary outcome of this study is the guideline-concordant rate of pRBC transfusions. The primary objective of this study is to compare the group using the new interface (arm 1) versus the two groups using the new interface with interruptive or non-interruptive alerts (arms 2 and 3, combined). The secondary objectives compare guideline-concordant transfusion rates between arm 2 and arm 3 as well as comparing all of arms of the study in aggregate to historical controls. This trial concluded after 12 months on April 5, 2022.

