## Trial status

This trial is currently closed. The trial was originally intended to run for 12 months; however, the 6-month interim analysis revealed a lower number of transfusions than expected; thus, we elected to extend the trial to 18 months. However, at the next 6 months (week 52–July 2022), we achieved adequate sample size. Since this 12-month interim analysis completed in July 2022 suggested very strongly that there was no statistical significant difference between the arms, the trial was stopped on the original time frame of 52 weeks. All investigators will have access to the final trial dataset. Investigators plan to communicate trial results to the public via journal publication.

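### The interrupted time series lists no calendar-period error term and no seasonal term, so if the whole hospital varies from month to month, the step's standard error is too small

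*Protocol article*

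**What the plan says.** The model for the historical comparison is in the protocol article, Treatment comparisons. It uses "generalized linear mixed models with the binary outcome of guideline-concordant order (yes/no"). The section continues: "We will implement an interrupted time series analysis by parameterizing this model with fixed effects including an intercept", followed by "a term for post-trial onset (intercept shift), a linear time trend, and an interaction between post-trial onset and linear time trend (slope difference"). The random effects of this model are not named. The paragraph on the randomized comparisons does name its own: "group comparison(s) as a fixed effect, and a random intercept for provider".

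On the length of the series, the same section states "Pre-trial data is available for two years prior to the trial onset". Trial status reports that "the trial was stopped on the original time frame of 52 weeks". That gives 24 pre-trial and 12 post-onset months.

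On calendar shocks, the section says "The COVID pandemic likely affected the outcome of interest". If the effect on the pre-trial trend is notable, the immediate post-COVID period is to be left out of the pre-trial trend estimation. Neither the trigger nor the period is defined, and nothing comparable is said for the year after onset.

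On status, Study objective and outcomes and Treatment comparisons both call the comparison exploratory. The abstract's Methods paragraph lists it under the secondary objectives, as "comparing all of arms of the study in aggregate to historical controls".

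**The concern.** The step in an interrupted time series is judged from calendar periods. A model fitted to single orders with only a smooth trend in time treats each order as independent information about the step, given provider. If guideline concordance moves up or down for the whole hospital in a given month, the orders in that month are correlated. The number of orders then overstates how much is known. A provider intercept removes differences between providers, but not a shift that all of them share in the same month.

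Separately, a straight line through one post-onset year cannot represent an annual cycle. Part of any cycle is then attributed to the step or the slope change.

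This matters because all three arms received the general improvements, so those changes have no concurrent control. The time series is the only planned evidence on whether the new interface itself helped. Trial status says that the 12-month interim analysis pointed to no difference between arms. If the final primary test agrees, the plan does not open the arm 2 versus arm 3 test, and it compares the historical data with all arms combined.

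**Working it through.** The article gives no standard error, power or sample size for the time series, so there is no stated figure to reproduce. The check asks how often a two-sided 5% test of the step rejects when there is no true effect. The article states its 0.05 level for the primary and secondary comparisons; using it here is an assumption.

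**Inputs from Statistical power**
- About 30 orders a day, or 210 a week (about 910 a month).
- Hemoglobin is normal with mean 8.3 and SD 1. The order probabilities are 1, 0.2 and 0.08 for values below 7, from 7 to below 8, and 8 or more.
- The shares of encounters are 0.0968, 0.2853 and 0.6179. Concordant share of orders = 0.0968 / (0.0968 + 0.2 × 0.2853 + 0.08 × 0.6179) = 0.0968 / 0.2033 = 0.476.

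**Assumed, because the documents do not give it**
- Shared month shocks of SD s = 0.05 or 0.10 on the logit scale. In percentage points this is s × 0.476 × 0.524 × 100, or about 1.2 and 2.5.

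**Standard error of the step.** With a step and a slope change, the two segments are separate lines, and the step is their gap at onset. The end-point variance of a fitted line over n equally spaced points is about 4/n times the variance per point.
- Listed model: variance per week = 1 / (210 × 0.476 × 0.524) = 0.0191. Multiplied by (4/104 + 4/52) = 0.1154, this is 0.0022, so SE ≈ 0.047.
- Extra variance from month shocks: s² × (4/24 + 4/12) = 0.5 s². At s = 0.10 this is 0.0050, so the true SD is √0.0072 ≈ 0.085. At s = 0.05 it is 0.00125, so the true SD is √0.00345 ≈ 0.059.
- Rejection rate = 2Φ(−1.96 × 0.047 / true SD): about 28% at s = 0.10 and 12% at s = 0.05.

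**Simulation** of the listed fixed effects (104 pre-trial and 52 post-onset weeks, 210 orders a week, 2,000 replicates):

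| Month SD (logit) | Model SE | Actual SD of step | Rejection |
|---|---|---|---|
| 0 | 0.047 | 0.047 | 5.1% |
| 0.05 | 0.047 | 0.060 | 12.6% |
| 0.10 | 0.047 | 0.084 | 27.8% |

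Across 700-900 orders a month the rates are about 11-13% and 25-36%; the upper part of the second range comes from month shocks with lag-1 correlation 0.3. At 300 a month they are about 7-8% and 13-20%.

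**Does a provider effect cure it?** A within-provider linear model with 228 providers (200 replicates) rejected 11% and 26% of the time at the two shock sizes, against 4% with no shocks. It does not.

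**Season.** The assumed cycle is an annual cosine with no month shocks. With its peak 13 weeks after onset, amplitude 0.05 gives a spurious step of +0.07 logit and 33% rejection; amplitude 0.10 gives +0.14 and 86%. With the trough there instead, the sign reverses. With the peak at onset or 26 weeks later, there is almost no bias and rejection is about 4-7%.

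**After a remedy.** The remedy tested was monthly aggregation with a dispersion factor and one annual harmonic pair. Rejection was 2.7% with no calendar variation, 4.8% and 6.0% at the two shock sizes, and 3.8% and 3.5% at the two seasonal amplitudes. At s = 0.10 the SE rises from 0.047 to 0.097. With lag-1 correlation 0.3 between months, month-level dispersion alone leaves 6-12%, so residual autocorrelation must also be checked. The remedy with an explicit autocorrelation term was not simulated.

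**The case against.** The strongest reply is that a journal article condenses a longer plan. The fixed effects are introduced as including those listed, and the model is called mixed without naming its random effects. Seasonal and correlation terms could therefore sit in a document not shown. This stands against any reading that the model will contain nothing else; the text does not say so. It does not dispose of the point. The article chose to write out the parameterization, and as written that parameterization does not suit a series judged from about 36 months.

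A reader might also infer that the plan ignores calendar shocks. It does not: it names COVID and provides an exclusion. But that rule is conditional and covers only the pre-trial trend. If used, it also shortens the two-year pre-period that has to separate trend, season and step.

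A reader might further infer that a claim of improvement from the new order set would often be false. The documents do not support that. They give no month-to-month or seasonal variance, and with none the listed model holds its level. The seasonal bias is near zero at some phases. Trial status also reports fewer transfusions than expected at six months, and lower volume reduces the inflation.

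Finally, the comparison is exploratory in the body of the article. The randomized comparisons are concurrent and unaffected, and remain the trial's main inference.

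**Conclusion.** The point holds in a conditional form. The listed model names no calendar-period error term and no seasonal term, a provider intercept would not substitute for either, and the COVID rule does not reach the post-onset year. Where variation shared by all providers exists, the step's standard error is too small. At about 910 orders a month, the actual SD of the step is 1.3 times the model SE for month shocks of 1.2 points, and 1.8 times for 2.5 points. An annual cycle of 0.10 logit amplitude can add a spurious step of up to about 0.13-0.14 logit (3.2-3.5 percentage points, multiplying by 0.476 × 0.524), with size and sign set by its phase in April.

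These sizes rest on assumed variation. The article's support for such variation is qualitative: it says that COVID likely affected the outcome. The consequence is confined to the historical comparison. It matters more if the abstract's secondary label is followed than if the exploratory label in the body is.

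**What to change.** Keep the intercept, step, trend and slope-difference terms. Add a calendar-month random effect, or analyse monthly counts with overdispersion. Check for residual autocorrelation and allow for it if present. Add one annual sine/cosine pair. State the random effects of this model, including whether the provider intercept is kept.

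In the abstract, describe the historical comparison as exploratory, in line with Study objective and outcomes and Treatment comparisons.

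No new data are needed. The cost is wider intervals for the historical comparison. The added terms must also be estimated from about 36 months, or fewer if the COVID exclusion is applied.

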Interim analyses were conducted at 6 and 12 months to test the primary objective comparison. If a statistically significant result of a 20% reduction in potentially guideline discordant behavior with a significance level of 0.05, the trial would have been stopped early and we would have declared one arm superior to the other if needed—thus, we set the bar high (at least 20% effect size). For example, if the probability of potentially guideline discordant behavior was 0.5 in one group, a difference of 0.2 × 0.5 = 0.1 is the effect size. Study personnel noted in the author list ([name]) have access to the interim results and base trial termination on these analyses.

All providers with pRBC ordering privileges at the start of the trial were prospectively enrolled in the study. There were no specific plans to promote participant retention as participation in this trial is dependent only on clinical privileges at the trial center. All providers enrolled were considered 100% adherent to the study protocol as they receive their designated EHR intervention arm each time they order blood products outside of guidelines. If a provider left UCH, their data contribution was included in the study up until the time of their departure from the system.

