We first simulated provider encounters where the provider has the opportunity to order a transfusion. In the observed trial data, we observed transfusions—thus, encounters that do not lead to a transfusion will not be observed. We generated encounters for these providers for time *t* (where *t* is the length of time the trial runs). Then, for each patient encounter, we simulated the HGB value associated with that encounter. We next simulated whether or not an encounter resulted in a transfusion order, which is conditional on HGB value and based on SME feedback. Transfusions are considered potentially guideline discordant if HGB is >  = 7 (any number of units). To explore potential effect sizes of the intervention for the primary hypothesis that groups 2 and 3 have an identical reduction in potentially guideline discordant ordering compared to group 1 (10% reduction, 15% reduction, and 20% reduction), we then decreased the assumed probabilities for transfusion ordering for encounters with HGB >  = 7 by *e*, where *e* is in (0.9,0.85,0.8). Finally, we implemented a logistic regression where each observation is a transfusion order, the outcome is guideline compliance as described above, and a fixed effect for treatment group with 2 levels (group 1 versus groups 2 + 3 combined). We tested the significance of the two-level fixed effect treatment group term against a significance level of 0.05. We replicated this simulation for each potential effect size (10% reduction, 15% reduction, and 20% reduction). To explore the difference in estimated power under each effect size for varying lengths of trial time *t,* we conducted the simulation 2000 times for each potential trial time length *t*, where *t* was 10 weeks up to 50 weeks.

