For the primary objective comparison, we assumed that groups 2 and 3 (non-interruptive or interruptive alerts) had an equal probability of guideline-concordant transfusion ordering. Within this scenario, we examined three different effect sizes (the difference in the probability of guideline-concordant transfusion ordering). The first effect size (smallest) assumed a 10% reduction in the probability of a potentially guideline discordant transfusion order occurring. The second effect size assumed a 15% reduction in the probability of a potentially guideline discordant transfusion order occurring. The third effect size (largest) assumed a 20% reduction in the probability of a potentially guideline discordant transfusion order occurring. We conducted a simulation with 2000 replicates for each effect size to estimate the length of time required for the study to achieve 80% power.

Results from these simulations indicate that we will have 80% power to detect an effect size of 15% at 35 weeks and an effect size of 20% at 19 weeks. At 52 weeks, the power to detect an effect size of 10% is 64%. Since there was uncertainty in the expected effect size (no preliminary data available) and the smallest effect size explored would require longer than 52 weeks to achieve 80% power, the trial was designed a-priori to run for 52 weeks.

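### The 20% in the stopping rule and the 20% in the power calculation are on different scales, so the stopping bar is about twice the largest designed effect and the detectable effects are mislabelled

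*Protocol article*

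**What the plan says.** **Stopping rule.** The section *Trial design and randomization* refers to "a-priori specified stopping criteria, specifically a 20% effect size as described below". The section *Treatment comparisons* gives the detail: "Interim analyses were conducted at 6 and 12 months to test the primary objective comparison", with early stopping "If a statistically significant result of a 20% reduction in potentially guideline discordant behavior with a significance level of 0.05" is found. A worked example fixes the scale. With a probability of discordant behavior of 0.5 in one group, "a difference of 0.2 × 0.5 = 0.1 is the effect size". The authors add that the bar was set high on purpose.

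**Power calculation.** The section *Statistical power* simulates encounters, then hemoglobin, then whether an order is placed. To create an effect, "we then decreased the assumed probabilities for transfusion ordering for encounters with HGB" at or above 7, using multipliers 0.9, 0.85 and 0.8. The same section notes that "encounters that do not lead to a transfusion will not be observed", and the simulated test is a logistic regression on orders. The scenarios are then summarized, for example: "The third effect size (largest) assumed a 20% reduction in the probability of a potentially guideline discordant transfusion order occurring". In the same paragraph, a parenthesis defines effect size as the difference in the probability of guideline-concordant ordering, which is the trial's outcome. Stated power is 80% for 20% at 19 weeks, 80% for 15% at 35 weeks, and 64% for 10% at 52 weeks.

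**The concern.** Both figures are called a 20% effect size, and the article never converts one to the other. Orders placed below 7 g/dL are unaffected in the simulation. When discordant orders fall by 20%, the total number of orders therefore falls too, and the discordant share drops by much less than 20%. A reader who takes the two figures as one would think that the stopping bar equals the largest designed effect, and that the trial was sized for differences of up to about 10 points in the outcome. The second belief matters most. The section *Trial status* reports that the trial stopped at 52 weeks because the 12-month analysis suggested no difference between arms, and the designed effects are the yardstick for reading that result.

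**Working it through.** **Inputs (all from the Statistical power section).** Hemoglobin is Normal with mean 8.3 and SD 1. Ordering probabilities under the null are 1 below 7, 0.2 from 7 to below 8, and 0.08 at 8 or above. Providers are split 1:1:1, so arm 1 against arms 2 and 3 is 1:2. Two-sided testing at 0.05 is assumed.

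**Step 1: orders per encounter.**
- P(<7) = 0.0968, P(7 to 8) = 0.2853, P(≥8) = 0.6179.
- Concordant: c = 1 × 0.0968 = 0.0968.
- Discordant: d = 0.2 × 0.2853 + 0.08 × 0.6179 = 0.1065.

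**Step 2: discordant share of orders**, p(e) = e·d / (c + e·d).

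| Multiplier e | Share | Fall (points) | Relative fall |
|---|---|---|---|
| 1 | 52.4% | – | – |
| 0.9 | 49.8% | 2.6 | 5.0% |
| 0.85 | 48.3% | 4.1 | 7.8% |
| 0.8 | 46.8% | 5.6 | 10.6% |

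**Step 3: the stopping bar on the same scale.** 0.8 × 0.524 = 0.419, a fall of 10.5 points. Solving p(e) = 0.419 gives e = 0.656, a cut of about 34% in discordant ordering. The ratio to the largest designed effect is 10.5 / 5.6 = 1.9.

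**Step 4: does the stated power confirm the per-encounter reading?** I used a two-proportion power formula with 1:2 allocation.

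| Orders per week | 20% at 19 weeks | 15% at 35 weeks | 10% at 52 weeks |
|---|---|---|---|
| Stated | 80% | 80% | 64% |
| 210–245 (30–35 per day, 7 days) | 91–95% | 91–94% | 74–80% |
| 150 (30 per day, assumed 5-day week) | 80.1% | 79.2% | 59.2% |

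The stated figures are not fully reproduced; they imply about 150 to 168 orders per week. They do settle the scale. If the 20% had been a fall in the order share (52.4% to 41.9%), about 800 orders would give 80% power, which is 800 / 210 ≈ 4 weeks or 800 / 150 ≈ 5 weeks. The stated 19 weeks fits only the per-encounter scale. Steps 1 to 3 do not depend on order volume.

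**Step 5: chance that the rule fires when e = 0.8 is true.** I read the rule as requiring an estimated relative fall of at least 20% together with p < 0.05, and I count only the first condition, so these are upper bounds.

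P = Φ(−(p₂ − 0.8p₁)/SE), with SE² = p₂(1 − p₂)/n₂ + 0.64·p₁(1 − p₁)/n₁.

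At 26 weeks and 150 orders per week, N = 3,900, n₁ = 1,300 and n₂ = 2,600. The gap is 0.468 − 0.419 = 0.049 and SE = 0.0148, so z = −3.32 and P = 0.00045. At 210 and 245 orders per week P is 0.00004 and 0.00001. At 52 weeks it is about 0.000001 or less. A plain p < 0.05 test at 26 weeks would have 91% to 99% power for the same effect.

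**Step 6: sensitivity.** The article gives no between-provider variance, so these are assumptions.
- Log-normal provider SD of 0.3, 0.6 or 1.0 in discordant ordering: the rule fires about 0–0.5%, 2–3.5% or 12.5–15% of the time (simulated with 228 providers at 21 to 74 orders per day).
- The section's other inputs (15% of encounters below 7; ordering probability 0.05 above 8), with the remaining 85% split as in the Normal model: the share falls from 35.6% to 30.6%, or 13.9% relative. The rule fires about 6% of the time at 26 weeks and 1.4% at 52 weeks (150 orders per week, independent orders).

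**The case against.** **A high bar was intended.** The article says so, and nothing in it promises that the rule would fire under the designed effects. This stands: a demanding efficacy bar is a legitimate choice. A reader might infer that the rule was defective; the documents show only that its distance from the designed effects is hidden by a shared label.

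**Power for the stopping effect.** A reader might also infer that the trial lacked the stated power for the effect that would stop it. The opposite is true under independent orders. For a fall from 52.4% to 41.9%, power at 19 weeks and 150 orders per week is above 99.9%, so the stated 80% is conservative for that effect.

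**The simulation's scale is disclosed.** The text does say what is multiplied, and the simulated test is on orders. This stands for the method. It does not rescue the parenthesis that equates these effects with differences in the outcome probability.

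**The odds scale.** On odds the two figures coincide: the odds ratio at e = 0.8 is exactly 0.80, and the rule would then fire about half the time. The example of 0.5 and 0.1 rules this reading out.

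**The trial is closed.** Both interims are past, so the mismatch could only have cost an early efficacy stop. This stands, and it limits the remedy to reporting.

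**Conclusion.** The two 20% figures are different quantities, and the description of the power scenarios as 10%, 15% and 20% differences in the probability of concordant ordering is wrong. On the observed scale the designed effects are 2.6, 4.1 and 5.6 points, roughly half the size that the label suggests. The stopping bar of about 10.5 points is about twice the largest of them.

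These sizes rest on the simulation's hemoglobin distribution and ordering probabilities. The gap persists under the section's alternative inputs (13.9% relative against 20%). The firing chance of less than 0.1% is specific to the simulation's independent-order model; several percent, or up to about 15%, is possible under assumed clustering or the alternative inputs.

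A reader might go further and doubt the final analysis. The documents do not support that: the planned test, its outcome and its data are unaffected by this mismatch.

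**What to change.** - In the section *Statistical power*, restate the detectable effects as shares of orders: 52.4% against 46.8%, 48.3% and 49.8% for the 19-, 35- and 52-week figures, updated if the power simulation is re-run.
- Say there that the simulation counts only hemoglobin of 7 or above as discordant, whereas the section *Description of outcome* also counts orders with too many units, so these shares approximate the trial's outcome.
- Correct the parenthesis that calls the simulated effects differences in the probability of guideline-concordant ordering.
- In the results report, state that the stopping bar was on a different scale and about twice the largest designed effect, so that the no-difference conclusion is read against effects of about 3 to 6 points.
- Leave the interim threshold as it was. Changing it now would be post hoc.

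The cost is a few sentences and one recalculation. The downside is that the detectable effects look smaller on the outcome scale.
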